## Abstract

**Introduction::**

Stroke survivors are commonly at risk of functional decline, which increase their dependency in activities of daily living and eventually affects their motivation level, self-efficacy, and quality of life. Circuit exercise has been shown to be useful in enhancing functional performance and quality of life of chronic stroke survivors. There is a need to review the existing “usual circuit exercise” and develop a better approach, such as game-based circuit exercise. Training in enriched and fun environment may possibly further promote neuroplasticity. However, evidence on inducing fun element in the existing circuit exercise among stroke survivors is limited. Also, no studies are available to date which report the benefit of circuit exercise on stroke survivors’ self-efficacy and motivation level. Therefore, this study aims to assess the effectiveness of game-based circuit exercise in comparison to conventional circuit exercise on functional outcome (lower limb strength, postural stability and aerobic endurance), motivation level, self-efficacy and quality of life among stroke survivors. This study also aims to assess whether the outcomes gained from the 2 interventions could be sustained at week 12 and 24 post-trial.

**Methods::**

This is an assessor-blinded randomized control trial comparing 2 types of intervention which are game-based circuit exercise (experimental group) and conventional circuit exercise (control group). Based on sample size calculation using GPower, a total number of 82 participants will be recruited and allocated into either the experimental or the control group. Participants in the experimental group will receive a set of structured game-based exercise therapy which has the components of resistance, dynamic balance and aerobic exercises. While participants in the control group will receive a conventional circuit exercise as usually conducted by physiotherapists consisting of 6 exercise stations; cycling, repeated sit to stand, upper limb exercise, lower limb exercise, stepping up/down and walking over obstacles. Both groups will perform the given interventions for 2 times per week for 12 weeks under the supervision of 2 physiotherapists. Outcomes of the interventions will be measured using 30-second chair rise test (for lower limb strength), Dynamic Gait Index (for postural stability), 6-minute walk test (aerobic capacity), Intrinsic Motivation Inventory questionnaire (for motivation level), stroke self-efficacy questionnaire (for self-efficacy) and Short Form-36 quality of life questionnaire (for quality of life). All data will be analyzed using descriptive and inferential statistics.

**Discussion::**

This study will provide the information regarding the effectiveness of including game elements into circuit exercise training. Findings from this study will enable physiotherapists to design more innovative exercise therapy sessions to promote neuroplasticity and enhance functionality and quality of life among stroke survivors under their care.

**Trial registration::**

Australian New Zealand Clinical Trials Registry, ACTRN 12621001489886 (last updated 1/11/2021)

## Introduction

1

Stroke is a significant health problem and cause of disability among adults worldwide. It was reported that, in 2019 there were nearly 101 million prevalent cases of stroke and 143 million disability-adjusted life-years (DALYs) due to stroke globally.^[1]^ Generally, mortality rate of acute stroke has declined with the advancement of medical care; most countries now witness an increasing number of stroke survivors hence those living with disability.^[2]^ This increased prevalence of stroke-related disability which requires continuous and long-term rehabilitation and healthcare support places great burden on healthcare system in most countries especially in the developing region.^[3]^

Rehabilitation remains the mainstay of poststroke management, aiming to minimize impairment and disability, and improve functional independence among the stroke survivors. Physiotherapy, being a main part of the multidisciplinary rehabilitation program plays a vital role through the poststroke stages. Physiotherapeutic interventions for poststroke patients include therapeutic exercises, electrophysical agents, manual therapy, virtual reality therapy, mirror therapy, robotic therapy and special techniques such as motor relearning program and Bobath.^[4–7]^ The service is provided during hospitalization for acute and sub-acute stroke, and normally continued in out-patient settings once the stroke patient is discharged home.

Therapeutic exercise with a focus on task specific training is the most utilized physiotherapy modality for stroke survivors.^[8]^ It can be delivered either through individual or group session; with the group session normally conducted in a form of circuit class exercise. During circuit exercise session, a group of three or more participants is supervised by 2 to 3 physiotherapists in performing repetitive practice of a number of tasks which arranged in several workstations in sight of each other.^[4,9]^ Circuit exercise for poststroke patients is normally provided 2 to 3 times per week and continued for as long as 1 month or more postonset depending on the individual patient's needs.^[10–16]^

Circuit exercise has been found to improve stroke survivors’ functions and quality of life.^[10–16]^ However, the conventional form is seen as less enriched and lacking in fun. Training in enriched and fun environment can promote neuroplasticity, in addition to facilitate personalized motivation and cease stress and anxiety among stroke survivors.^[17–20]^ Nonetheless, no studies have incorporate design-for-fun games environment into the existing circuit exercise. Past studies about circuit exercise have also not included motivation and self-efficacy, 2 important determinants for recovery among stroke survivors^[21]^ in their assessment of intervention outcome despite the fact that stroke survivors frequently demonstrate decline in these component and affect their functional independence over time.^[21–26]^ There is a need to review the existing conventional circuit exercise and offer a more enriched environment by adding multisensory stimuli and cueing, limb integration and cognitive stimulation to further increased neuroplasticity potentials such as game-based circuit exercise.^[27]^ Therefore, the purpose of this study is to determine the effectiveness of game-based circuit exercise in comparison to conventional circuit exercise on functional outcome, motivation level, self-efficacy and quality of life among stroke survivors. This study also aims to assess whether the outcomes gained from the 2 interventions could be sustained at week 12 and week 24 post trial.

## Methods

2

### Study design and setting

2.1

This is an assessor-blinded randomized control trial which compare 2 types of intervention, namely game-based circuit exercise (experimental group) and conventional circuit exercise (control group). The study will be conducted at Hospital Putrajaya, a main referral center for stroke cases in Putrajaya, the federal administrative capital of Malaysia. Database of post-stroke patients which is maintained by the physiotherapy department of the hospital will be used to recruit participants adequately. The flow of the participants through the trial is as shown in the CONSORT diagram (Fig. 1).

**Figure 1 F1:**
[figure not shown]
Consort diagram of the study.

### Study participants

2.2

Eligible participants will be recruited by the main researcher using the following inclusion criteria:

1.Clinically diagnosed either hemorrhagic or ischemic stroke by a medical or neurology physician.2.Age 40 to 80 years old (to minimise risk of frailty which is prevalent in those above 80).^[28]^3.Able to perform basic activities of daily living such as walking and turning, stepping up and down steps with or without a walking aid and hold a glass full of water with the non-affected hand.

Exclusion criteria are:

1.Score below 20 on Montreal Cognitive Assessment (MoCA) which indicates the presence of cognitive impairment2.Presence of other neurology or medical conditions which limit physical function such as Parkinson's disease, severe musculoskeletal disorders, unstable angina or uncontrolled hypertension.3.Score 4 or more on a Modified Rankin Scale (4: moderate severe disability; 5: severe disability; 6: death)4.Attended by a home physiotherapist after discharged from in-patient setting or attending a traditional therapy.5.Has visual field defects

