### Participants’ allocation

2.3

Selected stroke survivors will be randomized into either game-based circuit exercise (experimental group) or conventional circuit exercise (control group) using a stratified randomization method, with the use of sealed opaque envelopes by an independent researcher. Stratification variables are age, consisting of younger (40–59 years) and older adults (60–80 years), and disability level, namely 1 (no significant disability), 2 (slight disability) and 3 (moderate disability). Using the sealed envelope system, recruited participants will be stratified according to the sequence of age and disability level. Participants are then alternately allocated into each trial group according to their age and disability level categories. In this way, both the game-based circuit exercise and conventional circuit exercise trial group will consist of participants with comparable age and disability levels.

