### Data analysis

2.8

All data will be entered into IBM Statistical Packages for Social Sciences (SPSS) version 25.0. Intention-to-treat (ITT) analysis approach will be used; all the recruited participants will be included in the outcome analysis. Using ITT approach, missing data will be replaced with “last observation carried forward.” Socio-demography and health profile of the participants will be analyzed descriptively and reported as frequencies (percentages) and mean (standard deviation) or median (inter-quartile range). The effects of the interventions will be analyzed using mixed model ANOVA and reported as main time, group and time-group interaction effects for each outcome variable. Level of significance is set as *P* < .05 for all results.

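### Time since stroke is not limited at entry, stratified on or included in the stated model; pre-specifying it as a covariate would cheaply recover a modest and uncertain amount of precision

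*Protocol article*

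**What the plan says.** Section 2.2 opens the inclusion list with "Clinically diagnosed either hemorrhagic or ischemic stroke by a medical or neurology physician". None of the other inclusion or exclusion criteria sets a time window. The only one that touches the stage of care excludes patients "Attended by a home physiotherapist after discharged from in-patient setting or attending a traditional therapy", which refers to the period after discharge without bounding it.

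The recruitment source in section 2.1 is equally open: "Database of post-stroke patients which is maintained by the physiotherapy department of the hospital will be used to recruit participants adequately". The abstract's introduction describes circuit exercise as "useful in enhancing functional performance and quality of life of chronic stroke survivors", but that is background evidence and not an entry limit.

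Section 2.3 states: "Stratification variables are age, consisting of younger (40–59 years) and older adults (60–80 years), and disability level", the latter in three levels. Section 2.8 states: "The effects of the interventions will be analyzed using mixed model ANOVA", with time, group and time-by-group effects reported for each outcome. No covariate is named. Section 2.6 gives four occasions: baseline, end of the 12-week intervention, and 12 and 24 weeks after trial completion.

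**The concern.** The comparison of interest is the time-by-group interaction, that is, whether the arms change differently. Patients soon after a stroke may still be improving whichever arm they are in, while patients years after onset may be stable. With both enrolled, part of the spread in individual change reflects recovery stage. The stated model leaves that part in the residual of the interaction test.

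The existing controls do not fully reach it. Comparison from baseline cancels stable differences in level but not differences in slope. Disability stratification balances current function, yet two patients at the same disability level, one recent and one long past the stroke, may have different expected change.

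At stake is some power in a trial of 82, and a realised between-arm difference in time since stroke that a reader could not assess unless it is reported.

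**Working it through.** **The plan's own figure.** Section 2.7 gives 82 participants (41 per arm) for 80% power at alpha 0.05, using the repeated-measures within-between interaction test. The article does not state the effect size or the correlation among repeated measures, so 82 cannot be reproduced from it. With four occasions and an assumed correlation of 0.5, it back-solves to f = 0.130. The steps below need only the 41 per arm and the nominal 80%.

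**Inputs.** n = 41 per arm, 80% power and alpha 0.05 (section 2.7); four occasions (section 2.6). The partial correlation r of time since stroke with change, given what the design already controls, is not in the documents. It is assumed to be 0.1, 0.3 or 0.5.

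**Step 1: chance imbalance.** The SD of the standardised between-arm difference in a covariate is sqrt(2/41) = 0.221. Under randomisation:
- P(|difference| > 0.3 SD) = 17%
- P(|difference| > 0.5 SD) = 2.4%
- 95% limits: ±1.96 × 0.221 = ±0.43 SD

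**Step 2: effect on the contrast.** The resulting shift in the group contrast, in SDs of change, has SD r × 0.221 and 95% limits ±1.96 × r × 0.221. It averages zero over randomisations and is already part of the unadjusted standard error.

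**Step 3: gain from adjustment.** A linear covariate removes a share r² of the residual variance. As a two-mean approximation to the interaction test, 41 per arm gives 80% power at d = 0.619, since 0.619 × sqrt(41/2) = 2.80 = 1.96 + 0.84. With the SD multiplied by sqrt(1 − r²), power at the same d is Φ(2.80/sqrt(1 − r²) − 1.96). The n per arm for 80% power is 41 × (1 − r²), rounded up.

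| Assumed r | SD of shift | 95% limits of shift | Variance removed | Power | n per arm for 80% |
|---|---|---|---|---|---|
| 0.1 | 0.02 | ±0.04 | 1% | 80.4% | 41 |
| 0.3 | 0.07 | ±0.13 | 9% | 83.6% | 38 |
| 0.5 | 0.11 | ±0.22 | 25% | 89.9% | 31 |

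**Step 4: cost of the term.** In the mixed model a time-constant covariate entered only as a main effect leaves the time-by-group test unchanged. It must enter with its interaction with time, which uses 4 − 1 = 3 df. Within-subject error df go from (82 − 2) × 3 = 240 to (82 − 3) × 3 = 237. In a comparison at one timepoint the cost is 1 df. Estimating the coefficient inflates the variance of the contrast by about 1/(82 − 4) = 1.3%, which the table ignores. At r = 0.1 the net effect is therefore roughly nil, and at r = 0 the loss is about 1.3%.

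**The case against.** The strongest objection is that this is advice and not a defect. A one-paragraph analysis section may leave covariates to an analysis plan that is not shown, and its silence does not say that the model will be unadjusted. Other baseline variables could be proposed with equal logic. Disability level is stratified, entry requires walking and stepping ability, and the test works on change, so the remaining r may be small. Most of this stands, and it limits the point to an optional improvement. What it does not remove is that open entry and the choice of strata are design decisions the article states, and that the named model effects leave slope differences by stage in the residual.

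Four stronger readings are tempting, and the documents do not support them.

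- **That the plan contradicts itself.** Chronic stroke is mentioned only when citing earlier evidence. The stated aim concerns stroke survivors without a stage limit, and the criteria match it.
- **That the contrast is biased by 0.13 to 0.22 SD.** Those are 95% limits of a chance shift at r = 0.3 and 0.5. Under randomisation the shift is covered by the standard error.
- **That one covariate would remove the noise and imbalance.** It removes only the share it explains linearly, r².
- **That adjustment is worth a fixed number of extra participants.** Any such figure rests on a correlation that the documents do not give.

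**Conclusion.** The point holds as a modest precision improvement. Time since stroke is unrestricted, unstratified and absent from the stated model, and the other design features control recovery stage only in part. Over the assumed range of r from 0.1 to 0.5, the gross gain runs from 0.4 to about 10 power points, and is about 4 points at r = 0.3. The true value is unknown.

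The result rests on three assumptions: r itself, the two-mean approximation to the interaction test, and allocation that behaves as random. Section 2.3 also describes alternating assignment within strata. If that were applied literally, balance on unstratified factors would depend on entry order, and the randomisation argument used here would be weaker.

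Nothing here calls for a change to eligibility or sample size, and the plan is not wrong as it stands.

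**What to change.** Leave eligibility, strata and sample size unchanged. Then:

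1. Record the stroke onset date at baseline from the clinical record. The article does not say that the physiotherapy department's database holds it.
2. Report the distribution of time since stroke by arm in the baseline table.
3. Before data are seen, pre-specify log(time since stroke) together with its interaction with time in the mixed model. Alternatively, use it as a covariate in a baseline-adjusted comparison at each timepoint. If an analysis plan already does this, a cross-reference in section 2.8 is enough.

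The cost is one baseline field and either 3 df for the interaction in the four-occasion model or 1 df in a single-timepoint comparison. The loss of precision is negligible if the covariate turns out not to be prognostic.

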### Participants’ allocation

2.3

Selected stroke survivors will be randomized into either game-based circuit exercise (experimental group) or conventional circuit exercise (control group) using a stratified randomization method, with the use of sealed opaque envelopes by an independent researcher. Stratification variables are age, consisting of younger (40–59 years) and older adults (60–80 years), and disability level, namely 1 (no significant disability), 2 (slight disability) and 3 (moderate disability). Using the sealed envelope system, recruited participants will be stratified according to the sequence of age and disability level. Participants are then alternately allocated into each trial group according to their age and disability level categories. In this way, both the game-based circuit exercise and conventional circuit exercise trial group will consist of participants with comparable age and disability levels.

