### Interventions

2.4

The interventions in this study will be conducted for 12 weeks. Game-based circuit exercise group will receive a set of exercise tasks consisting of a) resistance exercises including sit to stand, partial squat, step up down, hip raise and heel raise, b) balance exercises including figure of 8 walking, tandem walking, backward walking, walking with instruction and walking with sudden change direction and c) aerobic exercises including punching jab, hook, cross straight and combination punching maneuver with squat and kicking, which aim to improve muscle strength, postural stability and aerobic endurance.

This game-based circuit exercise will use a specially designed exercise board namely Checkercise board (Fig. 2). The design of the Checkercise is similar to the “snake and ladder” game board. To use the Checkercise board, the participants will first be required to place their counter on the space that indicates “start.” Then, they have to take a turn to roll a dice. Next, they have to move their counter forward by several spaces based on the number as shown on the rolled dice. Exercises to be performed by the participants will depend on where their counter land on the board each time the dice is rolled, as each space shows a different exercise task. There is also a possibility of being penalized during the exercise if their counter lands on “penalty spaces,” such as spaces which indicate “slide back a few spaces,” and “move to a certain board number.” The game-based circuit exercises are considered complete when participants arrive at a space that indicates “finish.” The main researcher will supervise the participants in performing the Checkercise board exercise in the group of 4 participants per session. Exercise duration in each space is 2 minutes interspersed by 2 minutes rest with a total of ten exercises to be performed in average for a duration of 40 minutes. Participants will perform the given exercises at a comfortable pace for 2 times per week, under close monitoring by the main researcher. Exercise adherence and the level of exercise intensity (e.g., low, moderate, vigorous) will be monitored using sessions attendance checklist and Borg Scale Rate of Perceived Exertion, respectively. Table 1 shows the frequency, intensity, time and type (FITT) principle of the Checkercise board exercises to be provided to participants in game-based circuit exercise group.

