### Assessment of outcomes

2.6

The baseline and therapy outcomes at the end of week 12 of interventions and at a follow up at week 12 and 24 of trial completion will be measured by a therapist who is blinded to the group allocation and trained to conduct the standardized tests. To avoid assessment bias, the recorded baseline assessment data will not be accessible to the blinded assessor during the post-trial and follow-up assessments.

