### Ethics and dissemination

2.9

This study received ethical approval from the National Medical Ethics and Research Committee (NMERC) (study ID: NMRR–20–2715–57464). NMERC, being an independent research committee under the Malaysia Ministry of Health is also responsible in monitoring the study progress. All participants will be asked to provide an informed consent prior to participating in the study by the main researcher. Participants are allowed to withdraw anytime during the study without providing an explanation. Participants’ personal data will be kept confidential. Investigators in this study will have access to the final trial dataset. The findings of this study will only be published in a peer-reviewed journal.

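### Allocation is described as alternation within strata, which is not randomisation and lets the recruiter foresee about 93% of assignments

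*Protocol article*

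**What the plan says.** Section 2.3 (Participants' allocation) of the protocol article says that participants will be randomised "using a stratified randomization method, with the use of sealed opaque envelopes by an independent researcher". The strata are formed from age, "consisting of younger (40–59 years) and older adults (60–80 years"), and from "disability level, namely 1 (no significant disability), 2 (slight disability) and 3 (moderate disability"). The section then explains how assignments are made: "Participants are then alternately allocated into each trial group according to their age and disability level categories". It adds that this is how the two groups will come to be comparable on age and disability, so alternation is presented as the balancing device itself.

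Three other sections show who could see or use the sequence:

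- **Recruitment (2.2):** "Eligible participants will be recruited by the main researcher using the following inclusion criteria".
- **Consent (2.9):** "All participants will be asked to provide an informed consent prior to participating in the study by the main researcher".
- **Delivery of the experimental arm (2.4):** "The main researcher will supervise the participants in performing the Checkercise board exercise in the group of 4 participants per session".

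Blinding is described only for the outcome assessor. Section 2.6 says outcomes "will be measured by a therapist who is blinded to the group allocation and trained to conduct the standardized tests".

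**The concern.** The label and the mechanism in section 2.3 contradict each other. Under alternation, the next assignment in a stratum is the opposite of the last one. An opaque envelope hides an assignment only if its content cannot be worked out beforehand, and here it can. Having an independent researcher handle the envelopes does not change that.

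Prediction is realistic in this trial. Eligibility screening (section 2.2) uses age and the modified Rankin score, and these appear to be the variables that define the strata. The recruiter therefore knows each candidate's stratum. By supervising the game sessions, the recruiter also knows who went to the experimental arm, and everyone else enrolled must be a control. Candidates come from a departmental database (section 2.1), which leaves room to choose whom to approach and when.

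What is at stake is selection bias at enrolment. Motivation, self-efficacy and quality of life are self-reported, and the chair-rise and walking tests depend on effort. If keener patients were steered to the game arm, even unconsciously, these outcomes would favour it. Assessor blinding does not prevent this, because the selection happens before any outcome is measured. The planned mixed-model ANOVA cannot correct for characteristics that were not recorded.

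**Working it through.** The plan states no figure for predictability, so there is none to reproduce. The inputs are all in the protocol article.

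| Input | Value | Source |
|---|---|---|
| Age levels | 2 | 2.3 |
| Disability levels | 3 | 2.3 |
| Participants, N | 82 (41 per group) | 2.7 |
| Allocation rule | alternation within category | 2.3 |

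**Number of strata.** S = 2 × 3 = 6.

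**Assignments fixed by earlier ones.** Under strict alternation in enrolment order, only the first assignment in each stratum can be unknown. The number determined is N − S.

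- All 6 strata filled, random start in each: 82 − 6 = 76, and 76/82 = 92.7%.
- Only 5 strata filled: 82 − 5 = 77, and 77/82 = 93.9%.
- Only 4 strata filled: 82 − 4 = 78, and 78/82 = 95.1%.
- Starting arm fixed and known: 82 of 82.

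**Expected correct guesses with 6 random starts.** 76 + 6 × 0.5 = 79, and 79/82 = 96.3%.

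**Comparison with random schemes.** These were simulated with N = 82 and six strata assumed equally likely. The recruiter is assumed to see all past allocations in the stratum and to know which block sizes are possible.

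| Scheme within strata | Certain in advance | Guessed correctly | Mean absolute difference in arm sizes |
|---|---|---|---|
| Alternation, random start | 93% | 96% | 1.2 |
| Fixed blocks of 4 | 30% | 69% | 1.7 |
| Random blocks of 2 and 4 | 10% | 71% | 1.5 |
| Random blocks of 4 and 6 | 6% | 68% | 1.9 |
| Simple randomisation | 0% | 50% | 7.2 |

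Random blocks keep nearly all of the balance that alternation was meant to provide and remove most of the certainty. Some guessability remains under any blocked scheme while the recruiter can see past allocations.

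**The case against.** The strongest reply has four parts.

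1. **Loose wording.** Section 2.3 also speaks of randomisation, sealed envelopes and an independent researcher, so the alternation sentence may be a careless description of a balanced envelope scheme. That is possible, but nothing in the text supports it. The sentence is a stated mechanism, not a detail left to a fuller document, so it needs correcting on either reading.

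2. **Timing.** The 93% assumes one-at-a-time allocation in enrolment order. Section 2.3 speaks of recruited participants being stratified and then allocated, and recruitment draws on an existing database, so batch allocation after recruitment is compatible with the text. The recruiter could not then use the next assignment when choosing whom to approach. This stands as a limit on the route to bias. Allocation would still not be random and would depend on the order of the list.

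3. **Who supervises.** The Abstract (Methods) says two physiotherapists supervise both groups, whereas section 2.4 names the main researcher for the game arm. The two places must be reconciled. If the main researcher did not supervise, knowledge of past allocations would be less direct. The non-randomness does not depend on this.

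4. **Predictability is not bias.** The 93% measures how foreseeable assignments are, not the distortion of any outcome. Adjustment for baseline could reduce imbalance in measured characteristics. Both statements are right. Preferential enrolment of keener patients is a plausible mechanism that the documents do not demonstrate, and its effect cannot be sized from them. It could not be ruled out afterwards either.

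**Conclusion.** The concern holds. The mechanism in section 2.3 is not randomisation, it contradicts the label given in the same section, and no other section repairs it. On the plain reading, at least 76 of 82 assignments (92.7%) are determined by earlier ones, and all 82 if the starting arm is fixed and known.

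That size rests on strict alternation in enrolment order and on a recruiter who knows the earlier allocations, which follows from the roles in sections 2.2, 2.4 and 2.9. Batch allocation, or a different supervisor, would weaken the route to selection bias but would not make the allocation random. This must be corrected before the trial can be reported as randomised.

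**What to change.** Delete the alternation sentence in section 2.3 and state how the sequence is actually generated and concealed:

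- a computer-generated 1:1 permuted-block list within each stratum, with randomly varying block sizes that are not disclosed to the recruiter. Sizes of 4 and 6 are slightly harder to guess than 2 and 4, and either is far better than alternation;
- the list prepared and held by the independent researcher in sequentially numbered, sealed opaque envelopes, one series per stratum;
- each envelope opened only after consent and baseline assessment are complete.

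Two tidying points belong in the same edit. First, section 2.2 excludes modified Rankin scores of 4 or more but not 0, while the disability strata in section 2.3 start at 1. A score of 0 needs a stratum, most simply by defining the lowest one as 0–1. Second, the Abstract and section 2.4 should agree on who supervises the game-based sessions.

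The cost is one rewritten paragraph and one generated list. The independent researcher and the envelopes are already planned, so no extra staff are needed. If participants have already been allocated by alternation, the report should say so and say how many.
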